### Procedure

The researcher will first approach physicians attending to potential participants individually to explain the study workflow using the participant information sheet and their involvement in the deprescribing process for the intervention group. Written informed consent will be obtained from the physicians. Consenting physicians will be asked to complete the baseline demographic form Fig 1.

**Fig 1 pone.0324565.g001:**
[figure not shown]
Flowchart on the five-steps of the physical-pharmacy partnership in deprescribing intervention.

The researcher will review potential participant’s electronic medical records (EMR), if available, on the day before their appointment. The researcher will first approach the physician attending to the potential participant to determine suitability for the study before approaching selected potential patients to explain the purpose of the study. If the individual agrees to participate in the study, they will be randomised to an intervention (deprescribing) or control group (usual care) in a 1:1 ratio using a computerized random number generator in Microsoft Office® Excel® (Washington, United States of America) [24]. Participants randomized to the control group will continue to receive usual care, where medications will be reviewed and prescribed by their physician. Meanwhile, patients in the intervention group will receive an in-depth medication review performed by a pharmacist, which will focus on identifying PIMs as opportunities for deprescribing. In the intervention arm, a registered pharmacist will perform medication reconciliation using a structured medication list. However, in the control group, physicians will rely on electronic medical records and routine medication history-taking. PIMs identified in the intervention group will be deprescribed using the P3ID intervention, as shown in Participants will be followed up over 6 months (Fig 2). To assess the primary outcome, the number of prescribed medications will be determined by reviewing the patient’s medications through EMR and patient interviews via telephone calls at 3 months and 6 months. Medication adherence will be assessed using PMAI-9 and HMAI-9 via telephone calls at 3 months and 6 months. All participants will be requested to record any adverse drug reactions (ADR) due to their prescribed medications. For those undergoing deprescribing, they will be informed about the potential of withdrawal-related adverse effects, such as the return of previous symptoms or other withdrawal reactions. They will be asked to monitor and record any such symptoms. and asked to record these symptoms or withdrawal reactions. They will also be advised to see a doctor if they feel unwell or notice any unexpected adverse effects after stopping the medication.

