### Outcome measures

The primary outcome of this study will be the total number of prescribed medications. Secondary outcomes measured will include the number of medications deprescribed, fall occurrence, falls rate, PMAI-9 and HMAI-9. Within the intervention arm, additional information will be obtained on PIM, number of PIM deprescribed, and patients’ and doctors’ satisfaction towards pharmacist services.

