Recruitment of participants at a specialist clinic from a single study site limits the generalizability of our results to wider secondary care settings in Malaysia and elsewhere. The results are primarily applicable to settings where multidomain falls risk assessment is already implemented in accordance with international guidelines. While many patients in falls clinics meet the inclusion criteria for deprescribing, managing these patients and determining the most appropriate medications to deprescribe can be complex and require careful prioritisation to avoid potential harm related to omission of crucial treatment drugs. Medications that affect balance or cognition such as sedatives or antihypertensives can be difficult to deprescribe because of withdrawal symptoms or perceived necessity for managing chronic diseases.

Withdrawal of medications for chronic conditions, such as blood pressure and glucose lowering agents, proton pump inhibitors and antipsychotics, may negatively affect disease or symptom control leading to the medication being restarted [34]. The successful implementation of the deprescribing process, therefore, does require systemic changes through multiple levels of healthcare practice [35].

Deprescribing often requires close collaboration within the multidisciplinary team. Therefore, this RCT will allow us to evaluate the effectiveness of the deprescribing intervention in a smaller, controlled setting with a limited group of healthcare professionals in a highly poly-pharmaceutical patient population in which adverse outcomes have already occurred and further adverse outcomes are likely. However, expanding the intervention to a larger scale can face challenges, including the need for broader acceptance from prescribers, standardized protocols, and better coordination of care, as fragmented communication between providers. Cost-effective evaluation would be invaluable to inform policy, and should be included in future studies.

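### Withdrawal reactions and symptom return are recorded only by patients undergoing deprescribing, so these effects cannot be compared fairly by randomised arm

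*Protocol article*

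**What the plan says.** The Procedure section (text after Fig 1) sets two recording rules. The first covers both arms: "All participants will be requested to record any adverse drug reactions (ADR) due to their prescribed medications". The second covers a narrower group: "For those undergoing deprescribing, they will be informed about the potential of withdrawal-related adverse effects", with recurrence of earlier symptoms given as an example, followed by "They will be asked to monitor and record any such symptoms". For the control arm the section says only this: "Participants randomized to the control group will continue to receive usual care, where medications will be reviewed and prescribed by their physician". It states no matching request about withdrawal or returning symptoms.

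Under Outcome measures, the main endpoint is a medication count: "The primary outcome of this study will be the total number of prescribed medications". The next sentence reads: "Secondary outcomes measured will include the number of medications deprescribed, fall occurrence, falls rate, PMAI-9 and HMAI-9". The extra items collected only in the intervention arm are PIMs, PIMs deprescribed, and patient and doctor satisfaction. Adverse drug reactions, withdrawal reactions and symptom return do not appear in either list.

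The Discussion nevertheless treats these effects as a real possibility. It says that withdrawing drugs for chronic conditions "may negatively affect disease or symptom control leading to the medication being restarted". It also expects the approach to reduce adverse drug reactions.

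**The concern.** A trial whose primary outcome is a drug count needs a fair view of what happens to patients whose drugs are stopped. The effects most directly tied to stopping are withdrawal reactions and the return of the symptoms that the drug was treating. As written, one group is told of these effects and asked to write them down. The other is asked only about reactions caused by drugs that they take.

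Control patients can also have drugs stopped. Every clinic patient has a medication review as part of the multidomain assessment, control physicians review medications, and the number of medications deprescribed is a secondary outcome that is not restricted to the intervention arm. Symptoms can also worsen in patients who have had nothing stopped.

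If recorded symptoms were tabulated by arm, the arm with more prompting would show more events even if the true rates were equal. That could make the intervention look harmful when it is not. If the records are set aside for that reason, a lower medication count cannot be weighed against symptom control.

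**Working it through.** **1. Who is asked what (Procedure; Outcome measures; Table 1)**

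| Item | Intervention arm | Control arm | Listed outcome? |
|---|---|---|---|
| Falls (diary, 3- and 6-month calls) | yes | yes | yes, secondary |
| Fall injuries (diary prompts) | yes | yes | not separately |
| Syncope symptoms (patient assessment form, baseline, 3 and 6 months) | yes | yes, no arm restriction stated | no |
| Reactions to drugs being taken | yes | yes | no |
| Withdrawal reactions, symptom return | if undergoing deprescribing | no request stated | no |

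Only the last row is unequal. The request in the row above does not fill the gap, because a symptom that returns after a drug is stopped is not a reaction to a drug being taken.

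**2. Two readings of the restriction**

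- *Only the intervention arm is meant.* The Procedure section labels that arm as the deprescribing arm, so this is the likelier reading. The arms are then asked different things by design.
- *Anyone whose drug is stopped is meant, in either arm.* The prompted group is then defined by an event after randomisation, and patients with nothing stopped are still not asked.

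Both readings fit one expression. Let p be the true symptom rate, equal in both arms; c1 and c0 the share of events recorded with and without prompting; f and g the share of intervention and control patients prompted. Taking p as the same in prompted and unprompted patients:

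spurious difference = p × (c1 − c0) × (f − g)

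The first reading has g = 0, and f = 1 if every intervention patient is prompted. The second has g above 0, but f exceeds g whenever the intervention works as intended. The difference vanishes only if f = g or c1 = c0.

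**3. The plan's own figure**

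The plan gives no figure for harms. The only figure used below is its 58 per group, which reproduces from the Sample size calculation: difference 1.9 + 0.1 = 2.0, SDs 4.1 and 3.5, two-sided 5%, 80% power.

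n = (1.96 + 0.8416)² × (4.1² + 3.5²) / 2.0² = 7.849 × 29.06 / 4 = 57.02, rounded up to 58.

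**4. Illustration (p, c1 and c0 are assumptions; f = 1, g = 0)**

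Recorded rate = p × c. With c1 = 0.8:

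- p = 0.20: 0.20 × 0.8 = 16%, against 0.20 × 0.5 = 10% or 0.20 × 0.6 = 12%. Difference 4 to 6 points, ratio 1.3 to 1.6.
- p = 0.30: 0.30 × 0.8 = 24%, against 15% or 18%. Difference 6 to 9 points.

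A wider range, with c1 = 0.9. The last column is the approximate chance that a two-sided 5% test of two proportions with 58 per arm is significant:

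| p | c0 | Recorded, prompted vs not | Ratio | Chance significant |
|---|---|---|---|---|
| 0.10 | 0.7 / 0.5 / 0.3 | 9% vs 7% / 5% / 3% | 1.29 / 1.8 / 3.0 | 6% / 13% / 27% |
| 0.20 | 0.7 / 0.5 / 0.3 | 18% vs 14% / 10% / 6% | 1.29 / 1.8 / 3.0 | 9% / 24% / 51% |
| 0.30 | 0.7 / 0.5 / 0.3 | 27% vs 21% / 15% / 9% | 1.29 / 1.8 / 3.0 | 11% / 35% / 72% |

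If f − g were 0.5 rather than 1, each spurious difference would halve. With equal capture (c1 = c0) the ratio is 1.0 and the error rate is the nominal 5%.

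**5. What equal asking would deliver**

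With 58 per arm and equal capture, 80% power needs a rise from 5% to about 23%, from 10% to about 31%, or from 20% to about 44%. The comparison would be fair but imprecise, which favours reporting intervals over relying on a test.

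**The case against.** The strongest reply is that the biased comparison is not one that the plan makes. No between-arm test of withdrawal symptoms appears under Outcome measures or Data analysis, and there is no safety hypothesis. The recording request reads largely as patient counselling. That is correct, and it limits the weight of the point. What remains is that the data for a fair comparison would not exist, and symptoms nobody asked about cannot be reliably recovered later.

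The article is also condensed. Adverse event forms and items such as deaths or hospital attendance may sit in the full protocol, so their absence is no finding. The list of secondary outcomes is introduced as what will be included, which may not be exhaustive. This could excuse the missing safety outcome. It does not excuse a recording rule that is stated and unequal.

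A reader might infer more than the text supports:

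- *That the trial cannot compare harm at all.* Falls are secondary outcomes collected by diary and calls without restriction by arm, and all participants are asked about drug reactions.
- *That Table 1 has no harm instrument.* The falls diary prompts for injuries, and the patient assessment form covers syncope symptoms at 3 and 6 months.
- *That every stopped drug counts as a success.* Medications are counted at 3 and 6 months, so a drug restarted by then re-enters the primary outcome.

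Finally, the restriction refers to patients undergoing deprescribing rather than naming an arm, so the exclusion of controls is an inference, though the likelier one. The point does not depend on it, because under neither reading are the two arms asked the same thing.

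**Conclusion.** The point holds for withdrawal reactions and symptom return, and no further. The Procedure section fixes an unequal recording rule for the effects that the Discussion itself warns about, and Outcome measures names neither these records nor the drug-reaction records as an outcome. A comparison of these records by randomised arm would be biased by prompting, most likely inflating the intervention arm.

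The size cannot be taken from the documents. Under the assumed rates above, the spurious excess runs from 2 to 18 percentage points (ratio about 1.3 to 3.0) with no true difference. It is smaller if only part of the intervention arm is prompted or if some controls are prompted too. These figures show direction, not an estimate. The primary analysis is unaffected. This is a cheap improvement, best made before more follow-up data are collected.

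**What to change.** In the Procedure section and Table 1, add a short structured set of questions to the 3- and 6-month telephone calls, worded identically for both arms: new or returning symptoms, drug reactions, and whether any stopped drug has been restarted. In Outcome measures, list these as safety outcomes, reported by randomised arm with risk differences and confidence intervals.

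Leave the counselling and self-monitoring of deprescribed patients unchanged, but do not use those prompted self-records for the comparison between arms. Equal questions remove the unequal asking. Counselled patients may still be more alert to symptoms, and the report should say so.

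The cost is slightly longer calls, one row in Table 1 and one line under Outcome measures. No extra contacts and no change in sample size are needed.

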**Fig 2 pone.0324565.g002:**
[figure not shown]
Consort flow diagram on participant recruitment and follow-up .

A monthly falls diary with daily entries will be used to record fall occurrences which will returned through conventional mail for 6 months from randomization. When participants will be contacted at 3 and 6 months by telephone to encourage complete diary returns, at the same time they will also be asked to report the presence of any fall in the preceding three months. The date of falls will also be established, and if the participant has problems recalling the exact date, the week or month of falls will be recorded.

### Outcome measures

The primary outcome of this study will be the total number of prescribed medications. Secondary outcomes measured will include the number of medications deprescribed, fall occurrence, falls rate, PMAI-9 and HMAI-9. Within the intervention arm, additional information will be obtained on PIM, number of PIM deprescribed, and patients’ and doctors’ satisfaction towards pharmacist services.

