**Conclusion:**

The P3ID trial tests the hypothesis that a jointly led pharmacist-physician intervention in an outpatient will reduce the total number of medications, improve medication adherence, reduce falls and improve patients’ and doctors’ satisfaction towards pharmacist services. Findings from this study would inform future deprescribing practices, particularly in LMIC, pertaining to fall prevention as well as aid the development of future deprescribing interventions in other settings.

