The concept of deprescribing concept is also now increasingly popular among clinicians as a formalised approach to improving medication safety for older persons. Based on a feasibility study conducted using a physician-pharmacist partnership intervention developed in a primary care setting, deprescribing was successfully performed in 53% of PIMs found in older persons attending the clinic [10]. A systematic review found that deprescribing was safe and reduced number of medications as well as improved health-related quality of life (HRQOL), reduced healthcare costs, and hospitalization [11]. However, despite these promising outcomes, the review also highlights a critical gap: most of the evidence comes from high-income countries, with limited data available from low- and middle-income countries (LMICs). Furthermore, the lack of prospective outcome data on deprescribing in outpatient settings—where the majority of older persons are managed—remains a significant barrier to widespread implementation, particularly in resource-limited settings. This underscores the importance of evaluating deprescribing interventions in LMICs. By generating local evidence on its effectiveness in improving clinical outcomes and reducing medication burden in older adults, particularly in the falls and syncope clinic, this study will provide critical insights into how deprescribing can be optimized and scaled in LMIC contexts. Hence, our study aims to determine the effect of a Pharmacist-Physician Partnership Intervention for Deprescribing (P3ID) on reducing the total number of prescribed medications among older adults attending a falls and syncope clinic. In addition, the secondary outcomes of medication adherence, fall occurrence, rate of falls and patients’ and doctors’ satisfaction will also be evaluated.

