### Instruments used

The instruments used for this study are described in detail in Table 1. Each instrument is outlined based on its purpose and the specific data it collects.

**Table 1 pone.0324565.t001:** Instruments used and timepoints.

No	Instruments	Description	Instruments to be completed by	Time-points
1	Baseline demographic questionnaire	to collect doctors’ demographic data	Physicians, patients	Baseline
3	STOPPFall	to analyse patients’ medication list for any PIMs.	Pharmacist	Baseline
4	Patient-Medication Adherence Instrument (PMAI-9)	to assess patients’ adherence towards their medications from the patient’s perspectives	Patients	Baseline, 3 month, 6 month
5	Healthcare-Professional-Medication Adherence Instrument (HMAI-9)	to assess patients’ adherence towards their medications from and HCP’s perspectives	Pharmacist	Baseline, 3 month, 6 month
6	Patient assessment form	to document the medical history, medication history, falls history, syncope symptoms and its precipitating factors, clinical frailty scale score and deprescribing intervention in older persons.	Pharmacist	Baseline, 3 month, 6 month
7	Ambulatory Care Patient Satisfaction Questionnaire (ACPSQ)	to assess quality of pharmacy services delivered by the pharmacist.	Patients	Baseline
8	Physician–Pharmacist Collaborative Index (PPCI)	to assess the professional exchanges between doctors and the pharmacist.	Physicians	Baseline
9	Falls diary	to record any falls occurrence in older persons. Prompts will be provided in the falls diaries, which include how and when a fall occurred, or if there were injuries sustained after their fall.	Patients	Daily (Diary returns at 3 month and 6 month)

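### The trial claims to test whether the intervention improves patients' and doctors' satisfaction, but one satisfaction score at Baseline, collected within the intervention arm, cannot show improvement

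*Protocol article*

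**What the plan says.** Four places in the protocol article bear on satisfaction.

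- **Abstract, Conclusion.** Among the effects that the trial is said to test is that the intervention will "improve patients’ and doctors’ satisfaction towards pharmacist services".
- **Introduction, last sentence.** Satisfaction is one of the secondary outcomes: "the secondary outcomes of medication adherence, fall occurrence, rate of falls and patients’ and doctors’ satisfaction will also be evaluated".
- **Outcome measures.** The list of secondary outcomes does not contain it: "Secondary outcomes measured will include the number of medications deprescribed, fall occurrence, falls rate, PMAI-9 and HMAI-9". Satisfaction follows in a separate sentence: "Within the intervention arm, additional information will be obtained on PIM, number of PIM deprescribed, and patients’ and doctors’ satisfaction towards pharmacist services".
- **Instruments used, Table 1.** ACPSQ is completed by patients and serves "to assess quality of pharmacy services delivered by the pharmacist". PPCI is completed by physicians and serves "to assess the professional exchanges between doctors and the pharmacist". The only time-point entered for either is Baseline. In the same table PMAI-9, HMAI-9 and the patient assessment form are each entered at baseline, 3 months and 6 months.

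**The concern.** To say that something improved, one needs a comparator: an earlier score in the same people, or a score in people who did not get the intervention. Restricting satisfaction to the intervention arm removes the second. Scheduling each instrument once removes the first. A stated hypothesis is then left without the data to answer it, and an analysis plan cannot supply data that the schedule does not collect.

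Two things are at stake. The final report could claim improved satisfaction on the strength of a single favourable score. And if the sponsor does want an answer, follow-up scores cannot be recovered once the trial has ended. The sections also disagree on whether satisfaction is a secondary outcome at all.

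**Working it through.** The plan gives no effect size, standard deviation or sample size for ACPSQ or PPCI, so there is no figure to reproduce. The stated 58 per group (70 recruited per arm) is derived for the number of medications and has no bearing here. The check is a count of the contrasts that the schedule makes available.

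**ACPSQ (patients)**
- Arms measured: 1 (intervention; Outcome measures).
- Time-points: 1 (Baseline; Table 1).
- Between-arm contrasts: 1 arm − 1 = 0.
- Before-after contrasts: 1 time-point − 1 = 0.

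**PPCI (physicians)**
- Time-points: 1 (Baseline; Table 1), so before-after contrasts: 1 − 1 = 0.
- Between-arm contrasts: none exist by design. The Procedure section randomises patients. Physicians are recruited and consented but not described as randomised, and nothing stops one physician from treating patients in both arms. For PPCI the realistic contrast is before versus after, and the single time-point removes it.

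**Does the timing of Baseline matter?** Table 1 does not say whether the two questionnaires come before or after the pharmacist's review.
- If before, the patient has not yet received the service to be rated, and nothing later is collected.
- If after, the score describes satisfaction with the review, but there is nothing to set it against.

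Either way there is one score per person, and no change can be estimated.

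**Does the Data analysis section help?** It plans no hypothesis tests on baseline variables. It compares variables measured once by logistic or linear regression. With satisfaction collected in one arm there is no group term to fit. A regression on patient characteristics within that arm would describe who is more satisfied, not whether the intervention raised satisfaction.

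**Is a single entry just shorthand?** Table 1 writes out 3 and 6 months for three other instruments, so the authors list repeat measurements where they intend them.

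**The case against.** The best defence is that the methods already treat satisfaction as descriptive. The claim of improvement stands in one sentence of the abstract. The Introduction promises only that satisfaction will be evaluated, which a one-arm description meets. Outcome measures puts it under additional information, outside the secondary outcome list, and the article's closing Conclusion restates only the primary outcome. On this view the fault is loose wording. That is a fair account of where the fault lies, and it is why rewording is a full remedy. It does not remove the conflict: the abstract states a hypothesis that the schedule cannot answer, and the Introduction does call satisfaction a secondary outcome.

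The one-arm restriction is also defensible. Controls receive usual care, with medications reviewed by their physician, and no study pharmacist review is described for them. A rating of the pharmacist's service would have no clear object. This stands, and the restriction is not a fault in itself. It becomes a problem only when joined to a hypothesis of improvement and a single time-point.

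Figures 1 and 2 are not available here and might show the sequence of steps. If either showed a later satisfaction measurement, it would conflict with Table 1 and still need reconciling.

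Two stronger readings are tempting, and the documents support neither.
- **The scores are useless because they precede the pharmacist's work.** Table 1 also lists the pharmacist's STOPPFall screen at Baseline, so that label covers at least part of the pharmacist's work, and ACPSQ is described as rating services delivered. A rating after the review is plausible and would give usable descriptive data.
- **Control-arm data are missing for both instruments.** For PPCI there is no randomised control group of physicians to be missing.

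**Conclusion.** The point holds as an inconsistency between a stated hypothesis and the measurement schedule. As written, ACPSQ and PPCI each supply 0 before-after and 0 between-arm contrasts, so they can describe satisfaction and cannot show that it improved. A larger sample would not change this.

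The conclusion rests on reading Table 1 and Outcome measures as they stand. It does not depend on where within the baseline visit the questionnaires fall.

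The issue is moderate and limited to satisfaction. A reader might infer that the trial's main conclusions are in doubt; they are not. The number of prescribed medications, falls and adherence have their own follow-up schedules and are untouched.

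**What to change.** Choose one of two routes and make the abstract, Introduction, Outcome measures and Table 1 agree.

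**(a) Reword.** Remove improved satisfaction from the hypothesis in the abstract, bring the Introduction into line with Outcome measures, and state that ACPSQ and PPCI will be reported descriptively only. This costs nothing.

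**(b) Measure again.** In Table 1 add a post-intervention time-point: ACPSQ at the 6-month telephone call that is already planned, and PPCI for physicians at trial end. State whether the Baseline score is taken before or after the pharmacist's review, since the meaning of a change depends on it. Report the change as an uncontrolled before-after difference, without causal language, because time and growing familiarity could produce it too. The cost is one short extra questionnaire for patients and one for physicians.

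If a between-arm comparison of ACPSQ is wanted, give it at 6 months to all randomised controls. Giving it only to controls who had contact with pharmacy services would select on an event after randomisation, and the comparison would no longer be a randomised one. What a control patient is being asked to rate would need to be defined first.
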